## Abstract

**Background:**

This study protocol evaluates the effectiveness of adjuvant electroacupuncture (EA) for urinary retention in poststroke patients undergoing conventional treatments, in comparison with that of a sham control.

**Methods/design:**

A multicenter, blinded, randomized controlled trial will be conducted in three hospitals in the Republic of Korea. We are recruiting 54 stroke survivors (aged >19 years), who were diagnosed with urinary retention based on the results of two consecutive post-void residual (PVR) tests, and dividing them randomly into two arms: the EA and Park-sham control groups.

They will receive ten sessions of EA or sham treatment for 2 weeks. The participants will be blinded with non-penetrating needles and fake sounds of EA stimulators. The daily PVR ratio will be primarily measured at baseline and at the end of the study to statistically test the effectiveness of EA for poststroke urinary retention. Then, the Korean version of the Qualiveen Questionnaire, the Korean version of the International Prostate Symptom Score, and the blinding index will be assessed. After each EA session or sham EA, adverse events will be reported to evaluate the safety of EA.

Results will be analyzed by using the independent *t*-test or Mann-Whitney *U* test, based on both intention-to-treat and per-protocol principles.

**Discussion:**

The findings will provide clinical evidence for the effectiveness of EA treatment to improve urinary retention in stroke survivors.

**Trial Registration:**

This study protocol was registered in ClinicalTrials.gov (NCT02472288) on 10 June 2015.

## Background

Urinary retention (UR) or incomplete bladder emptying (IBE), defined as a post-void residual (PVR) urine volume of >100 mL on two consecutive occasions [1, 2], occurs in approximately 29 % [1] to 56 % [3] of poststroke patients. Bladder problems that occur after stroke episodes deteriorate the stroke survivors’ quality of life (QoL) and affect their disability and mortality [4–6]. UR in stroke survivors is usually managed with catheterization, but this procedure interferes with their active rehabilitation and can induce urinary tract infection (UTI) [2]. In the long term, UR without adequate management can lead to renal dysfunction [7]. Thus, caregivers should provide poststroke patients who have UR with proper bladder management to improve the patients’ functional outcomes [8].

In the United Kingdom, sacral neurostimulation has been known to be effective for UR induced by urethral sphincter overactivity (Fowler’s syndrome). However, significant complications have occurred, such as inserted lead migration or high surgical revision rates [9]. Bladder problems have also been a concern of traditional medicine practitioners. Diabetic bladder dysfunction was improved with acupuncture treatment in a pilot study [10]. Another randomized controlled trial showed that, besides sham electroacupuncture (EA), EA is an effective treatment of bladder muscle overactivity in poststroke patients [11]. A small-scale of clinical study with a single study group suggested the potential benefit of EA therapy for poststroke patients with IBE.

However, randomized controlled trials designed with adequate statistical power and sham comparators should be conducted to determine whether EA is effective for poststroke UR. We will conduct a multicenter, randomized controlled trial to evaluate the effectiveness of adjuvant EA therapy for poststroke patients with UR who are undergoing conventional treatments, in comparison with that of sham EA.

## Methods/design

### Study design

This is a multicenter, blinded, randomized controlled trial to compare an EA group with a sham EA group, with an allocation ratio of 1:1. We designed the protocol, conforming to the Consolidated Standards of Reporting Trials (CONSORT) [12] and Standards for Reporting Interventions in Clinical Trials of Acupuncture (STRICTA) [13] guidelines. The study process is illustrated in Fig. 1. The institutional review board of Kyung Hee University Korean Medicine Hospital approved the study (KOMCIRB-150213-HR-005). The protocol has been registered in ClinicalTrial.gov (NCT02472288).

**Fig. 1 Fig1:**
[figure not shown]
Flowchart of the study process. Fifty-four participants will be randomized and allocated to either the intervention or control group. After conducting ten sessions of verum or sham electroacupuncture for 2 weeks and examining for urinary tract infection (UTI), the daily post-void residual (PVR) ratio, Korean version of Qualiveen Questionnaire score (K-QQ), Korean version of the International Prostate Symptom Score (K-IPSS), and blinding index (BI) will be measured. Adverse events will be investigated right after each session

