### Interventions

The EA and sham EA regimens are based on traditional Korean medicine. We referred to the textbook [14] and consulted acupuncture and stroke specialists.

The participants allocated to the EA group will receive five sessions per week of EA therapy for 2 weeks (ten sessions in total). After inserting needles (stainless steel, 0.25 mm in diameter and 4.0 mm in length; Dong Bang Acupuncture Inc., Republic of Korea) using the Park-sham guide tube on bilateral acupoints BL31, BL32, BL33, and BL34 (eight points in total) at 5–10 mm in depth, the *de qi* sensation is elicited. The locations of the acupoints according to the World Health Organization Standard Acupuncture Point Locations in the Western Pacific Region are illustrated in Fig. 2 [15]. *De qi* means an acupuncture needle sensation of soreness, tingling, fullness, ache, coolness, warmth, and heaviness, and a radiating sensation at and around the acupoints to the point of a threshold that elicits nerve impulse transmission to the cerebral cortex [16]. Then, electrostimulation will be administered for 20 minutes at a moderate frequency of 30 Hz (STN-111, Stratek, Republic of Korea).

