### Primary outcome

To evaluate the effectiveness of EA treatment over the sham device for poststroke UR, we will primarily assess the change in daily PVR urine ratios between the baseline and end point of the last session. The daily PVR ratio is computed by dividing the daily PVR urine volume by the daily PVR urine volume plus spontaneous voiding volume. The daily PVR urine volume for 24 hours will be examined with ultrasonography scanning. If the PVR urine volume is more than 100 mL, the residual will be removed through intermittent cauterization before the scanning. When spontaneous urination is impossible, a 24-hour weight change in diaper will be measured for the self-voiding volume.

If the urinary tract is infected at the end, the outcome assessor will measure the PVR urine volume on the third day of the last session after anti-UTI treatment for 48 hours. Otherwise, PVR urine volume will be measured on the next day of the last session.

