The patient-rated outcomes will not be measured when the participants are unconscious. The two caregivers with more than 1 year of practical experience, after being educated about the scales, will independently fill in the scales for the participants with low cognitive function and the discrepancy will be settled through discussion.

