### Safety assessment

Adverse events will be reported to evaluate the safety of EA for poststroke patients with UR. The questionnaires will be administered to the participants after every verum or sham EA session, and the results will be recorded and analyzed. The outcome assessors will judge the severity (mild, moderate, or severe), seriousness, and causality (definitely related, probably related, possibly related, possibly not related, definitely not related to the intervention, or not assessable).

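### The only adverse-event enquiry described comes right after each session, so events first appearing after a patient's last session have no described collection point

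*Protocol article*

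**What the plan says.** Three places in the Protocol article fix when adverse events are sought, and they agree.

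- Abstract, Methods/design: "After each EA session or sham EA, adverse events will be reported to evaluate the safety of EA".
- Fig. 1 caption: "Adverse events will be investigated right after each session".
- Safety assessment: "The questionnaires will be administered to the participants after every verum or sham EA session". The same section names who grades the events: "The outcome assessors will judge the severity (mild, moderate, or severe), seriousness, and causality".

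The Fig. 1 caption lists the end-of-treatment measures (infection check, residual ratio, the two scales and the blinding index) apart from adverse events, which have their own time point.

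The Primary outcome section sets a contact after the last session. With a urinary tract infection, "the outcome assessor will measure the PVR urine volume on the third day of the last session after anti-UTI treatment for 48 hours". Without one: "Otherwise, PVR urine volume will be measured on the next day of the last session".

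The end of the Secondary outcome section gives a rule for participants who cannot respond. It begins "The patient-rated outcomes will not be measured when the participants are unconscious" and goes on to have two trained caregivers complete the scales where cognitive function is low. Adverse events are not mentioned there.

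**The concern.** A questionnaire given as the session ends sees what has happened by then. Bruising, delayed pain or infection at a needle site may show only hours later. In a patient who comes back, the next questionnaire can pick this up. After a patient's final session there is no next questionnaire, and the article describes no later enquiry. The final session is session ten for completers and an earlier one for patients who stop.

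This matters because the article reports adverse events in order to evaluate the safety of electroacupuncture. A patient who stops because of a delayed event is among the most informative for that purpose, and under the described schedule is also one whose event may not be recorded. The sham needle does not penetrate the skin, so among the study treatments penetration injuries can occur only in the active arm. Missing a late one loses a case from that arm.

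**Working it through.** The article states no adverse-event rate, so there is no plan figure for this point to reproduce. The check compares the stated time points, then illustrates the effect under labelled assumptions.

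**1. Which events meet a later enquiry**

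| Event first appears | Next described enquiry | Contact available |
|---|---|---|
| After one of sessions 1 to 9, patient returns | Questionnaire at the next session, if it asks about the interval | Yes |
| After session ten | None | End-point residual measurement, next day or third day |
| After the last session of a patient who stops | None | None described |

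The caption fixes when the question is asked. The period that the question covers is not stated.

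**2. How many patients might stop**

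Inputs from the Sample size section: 42 evaluable in total (21 per group), 20% dropout, 27 recruited per group. 21 / (1 − 0.20) = 26.25, rounded up to 27, and 2 × 27 = 54, so the plan's figure is reproduced. The margin is 54 − 42 = 12 patients (20% of 54 is 10.8). Under Data analysis, any of them with at least one session is in the intention-to-treat set.

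**3. Share of events lost (assumptions, not document figures)**

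Let d be the share of events that first appear after the questionnaire of the session that caused them. Suppose events are spread evenly over sessions and each questionnaire catches everything since the previous one. Then:

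- a completer loses d × 1/10 of events, at most 10% even if d = 1;
- a patient who stops after k sessions loses d/k, and more if the event itself caused the stop;
- if the questionnaire covers only the session just ended, the loss is d in either case.

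The documents give no value for d.

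**4. What under-capture does to the comparison**

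Assume true risks of 20% (electroacupuncture) and 10% (sham), 27 patients per arm, and a chance c that a patient with an event is counted.

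| c | Expected active-arm cases, 27 × 0.20 × c | Same c in both arms: difference 0.10c | Same c: ratio | c in active arm only: difference 0.20c − 0.10 | Active only: ratio 0.20c / 0.10 |
|---|---|---|---|---|---|
| 1.0 | 5.40 | 0.100 | 2.0 | 0.10 | 2.0 |
| 0.9 | 4.86 | 0.090 | 2.0 | 0.08 | 1.8 |
| 0.75 | 4.05 | 0.075 | 2.0 | 0.05 | 1.5 |
| 0.5 | 2.70 | 0.050 | 2.0 | 0.00 | 1.0 |

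Equal under-capture lowers the counts and the risk difference and leaves the risk ratio alone. The ratio moves only if the lost events are unequally divided between arms. For completers whose questionnaires do cover the interval, step 3 puts c at 0.9 or above. The lower rows need a questionnaire limited to the session just ended, or patients who stop early.

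**The case against.** The strongest reply is that a condensed article does not describe every route of reporting. Nothing in it says that the questionnaire is the sole source of events; the causality scale runs down to events definitely unrelated to treatment, which suits general recording; and spontaneous reports and follow-up may be set out in the full protocol. This stands against any claim that late events will be ignored. It does not remove the point, because the article goes beyond silence: it states a time point three times and, in the Fig. 1 caption, sets it apart from the end-point measures.

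Three stronger readings are tempting, and the documents do not support them.

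- *Unconscious participants give no adverse-event data.* The rule in the Secondary outcome section concerns patient-rated outcomes and does not name adverse events, which have their own section and are graded by assessors. Entry also excludes a Glasgow Coma Scale score below 8. What remains is that no one is named to answer the questionnaire for a participant who cannot.
- *Electroacupuncture will look safer than it is.* Collection is the same in both arms. A distorted ratio needs delayed events that are unequally divided between arms, and the article has no data on that.
- *Urinary complications are missed.* Urinalysis for infection is required in both groups before the end-point measurement, so the main such complication is already sought in completers.

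It is also fair to say that the gap is short for completers and that the trial's main objective is effectiveness.

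**Conclusion.** The point holds as a gap in a stated schedule; no passage contradicts another. Events first appearing after session ten, or after the last session of a patient who stops, have no described enquiry. For completers the open interval is one to three days and ends at a visit that already takes place. For patients who stop, it has no stated end, and the sample size leaves room for up to 12 of them.

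Delayed events may be undercounted, including penetration injuries that only the active study treatment can cause. The size cannot be derived from the documents, because it depends on the unknown share of delayed events and on the unstated recall period of the questionnaire. The conclusion rests on taking the stated timing at face value. If the full protocol already includes an end-point enquiry, only the article's wording needs to change.

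**What to change.** In the Fig. 1 caption and the Safety assessment section:

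- let the adverse-event window run from the first session to the end-point residual visit;
- word each questionnaire to cover the time since the previous one;
- have the blinded outcome assessor ask again at the end-point visit, or by one call to a patient who stops early;
- let the caregivers who already complete the scales answer for participants who cannot.

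The enquiry should stay with the assessor. Needle-site inspection by the treating practitioner is not advised: practitioners give the treatment and are not among those listed as blinded, so their findings could bring in detection bias.

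The cost is a form change with a short amendment, one call per patient who stops, and a slightly higher event count. Completers need no extra visit.

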### Participants

We will recruit 54 male or female patients aged ≥19 years from three hospitals in Korea: Kyung Hee Korean Medicine Hospital in Seoul, Cheonan Korean Medicine Hospital of Daejeon University in Cheonan, and Dongguk University Ilsan Oriental Hospital in Ilsan. In order to identify survivors from stroke episodes, like intracerebral hemorrhage or cerebral infarction, experienced practitioners will check the PVR urine volume twice a day. The patients will be pre-screened only if both residual volumes are >100 mL. After we obtain informed consent from the patients or their representatives, we will screen them according to the eligibility criteria for enrollment in the study.

### Inclusion criteria

We will include both male and female patients aged >19 years whose stroke episodes occurred within the last 2 years. We will not restrict inclusion of participants according to type of stroke or damaged region in the brain. Stroke history will be confirmed based on computed tomography or magnetic resonance imaging examination results. Two consecutive PVR tests will be performed, and the patient with the results of both residuals > 100 mL will be included in the trial [1, 2].

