### Exclusion criteria

We will exclude stroke patients with any one of the following clinical conditions from the medical screening process: (1) bleeding disorders, (2) procedures or surgeries for peripheral vascular diseases, (3) psychiatric disorders, (4) severe diseases in the lower urinary tract, (5) acute or chronic infectious diseases in the lower urinary tract, or (6) pregnancy (laboratory results from urinalysis). In addition, patients (7) whose medications for UR or relevant symptoms (urinary incontinence drugs or diuretics) have been changed within 3 days or (8) for whom onset of treatment is within 1 week prior to the study, along with those with a Glasgow Coma Scale score of <8 points, will be excluded. Finally, we will also exclude those who have fears about acupuncture therapy.

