### Randomization

Random sequences were generated separately in each site with the R package (R Foundation for Statistical Computing, Vienna, Austria, https://www.r-project.org) to allocate participants into either the EA or sham group. The allocation ratio was 1:1. From each center, at least 14 participants will be recruited, and the last 12 persons will be competitively enrolled among all the three sites. Only the delegated sub-investigators can access the security electronic file of the randomization table and assign the participants. Practitioners from each site will call or send a message to the sub-investigators in order to allocate the participants in their own hospitals. After assignments are completed, a sub-investigator from the primary site, Kyung Hee University Korean Medicine Hospital, will allocate the 12 participants from the three sites to the last participant. The investigators, who will generate the random number and assignments, will be blinded to the arm where each participant will be allocated.

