### Sample size

Based on a previous study [2], the mean percentage change in PVR ratios in the EA and control groups were computed. We assumed an after-treatment PVR ratio of 0.65 in the control group, as it was not reported in the study. The null hypothesis was that the percentage changes in PVR ratios have no significant difference between the intervention and control groups. With a significance level of 0.05 and a statistical power of 0.8, the calculated sample size in total was 42 [28]. Considering a 20 % drop rate at a 1:1 allocation ratio, we will recruit 27 participants for each group.

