### Data analysis

We will analyze results primarily based on the principle of intention - to - treat (ITT) and subordinately based on the per - protocol (PP) principle. The ITT analysis will include any participants who are randomly allocated and have at least one EA or sham session. Missing values will be imputed by the last observation carried forward. The PP analysis will cover only the patients who have at least seven sessions of EA or sham treatments and have no medical diagnosis of UTI at the end point.

Continuous variables will be tested by the independent *t*-test if normality is obtained. Otherwise, the Mann-Whitney *U* test will be implemented. The categorical variables will be analyzed by the Pearson *χ*^2^ test or Fisher's exact test.

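### Patients enter up to 2 years after stroke with no stated minimum, yet time since stroke is left out of the primary comparison: the test stays valid, but precision may be given away

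*Protocol article*

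**What the plan says.** All references are to the protocol article.

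- **Entry.** Inclusion criteria takes patients "whose stroke episodes occurred within the last 2 years". It sets no lower limit and adds: "We will not restrict inclusion of participants according to type of stroke or damaged region in the brain".
- **The one-week rule.** Exclusion criteria, item 8, removes patients "for whom onset of treatment is within 1 week prior to the study". The clock starts at an unspecified treatment, and the item follows one about changes in medication for retention. It is not clearly a limit counted from the stroke.
- **Randomisation.** "Random sequences were generated separately in each site with the R package". No other stratification factor is named.
- **Endpoint.** Primary outcome is the change in daily PVR ratio from baseline to the end of treatment. The Abstract gives the interval: "They will receive ten sessions of EA or sham treatment for 2 weeks".
- **Analysis.** Data analysis states: "Continuous variables will be tested by the independent" t-test if the data are normal, and otherwise by Mann-Whitney U. No covariate is named.
- **History items.** Other outcomes lists diabetes and benign prostatic hyperplasia, but not time since stroke.
- **Planning.** Sample size states: "We assumed an after-treatment PVR ratio of 0.65 in the control group", because the earlier study did not report it. It gives 42 evaluable patients and 54 recruited. It prints neither an SD nor the EA mean.

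**The concern.** The endpoint is a pre-to-post change, so any spontaneous change during the two weeks is part of it. The entry rule can place a recently affected patient and one at 20 months in the same comparison. If they tend to change at different rates regardless of arm, that difference becomes residual variance in an unadjusted test. A covariate could remove some of it.

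The planning source offers little reassurance. The Discussion describes the earlier study of EA for retention as a single-group study, so it had no control arm from which to learn how much untreated patients change or how much they vary.

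What is at stake is efficiency in a trial of 54 patients. The stroke date is needed anyway to apply the 2-year limit, so the information would be collected and then not used.

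**Working it through.** **1. The plan's own figure.** 42 evaluable is 21 per arm. With 20% dropout, 21 / (1 − 0.20) = 26.25, rounded up to 27 per arm, 54 in total. This reproduces, and so does the site arithmetic: 3 × 14 + 12 = 54. The 42 itself cannot be rebuilt, because the SD and the EA mean are not printed.

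**2. Implied effect.** Taking alpha 0.05 as two-sided (the article does not say), 21 per arm and power 0.80, the t-test gives a standardised difference d = 0.886. The normal approximation, (1.96 + 0.84) × √(2/21), gives about 0.865.

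**3. Assumed strength of the link.** Let R² be the share of variance in the change explained by time since stroke. The documents give no value. For illustration, take a residual SD of 0.20, a share p of early patients, and early patients improving by g more in both arms. Then R² = g²p(1 − p) / [g²p(1 − p) + 0.20²].

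| g | p = 1/3 | p = 1/2 |
|---|---|---|
| 0.1 | 0.05 | 0.06 |
| 0.2 | 0.18 | 0.20 |
| 0.3 | 0.33 | 0.36 |

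The range used below is therefore 0.05 to 0.36. The top of it is demanding: on this scale the implied treatment effect is 0.886 × 0.20 = 0.177, so g = 0.3 is about 1.7 times that effect.

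**4. Power at 21 per arm, two cases.** What adjustment achieves depends on what the unprinted planning SD contains.

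- *Case A: the planning SD already contains this variation.* Unadjusted power is 0.80. Adjustment shrinks the SD by √(1 − R²), so the standardised difference becomes 0.886 / √(1 − R²).
- *Case B: it does not.* The actual SD is larger, so the unadjusted standardised difference is 0.886 × √(1 − R²). Adjustment returns it to 0.886.

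| R² | A: unadjusted → adjusted | B: unadjusted → adjusted |
|---|---|---|
| 0.05 | 0.80 → 0.82 | 0.78 → 0.80 |
| 0.10 | 0.80 → 0.84 | 0.76 → 0.80 |
| 0.20 | 0.80 → 0.88 | 0.71 → 0.80 |
| 0.30 | 0.80 → 0.92 | 0.65 → 0.80 |
| 0.36 | 0.80 → 0.94 | 0.61 → 0.80 |

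These figures ignore the degree of freedom spent. Simulation of case B with an early/late term (8,000 trials per setting) gave adjusted power of 0.78 to 0.80.

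**5. The same at 27 per arm.** If all randomised patients are analysed, case A starts at 0.89. In case B, the same formula gives unadjusted power of 0.88, 0.82 and 0.72 for R² = 0.05, 0.20 and 0.36. It falls below the planned 0.80 only towards the upper end of the range.

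**6. Chance imbalance.** With 27 per arm, simple randomisation and an early share of 1/3 to 1/2, the exact binomial probability that the arms differ by 15 percentage points or more is 19% to 22%. With g = 0.2, a 15-point difference shifts the contrast by 0.2 × 0.15 = 0.03. The standard error of the contrast from residual variation alone is 0.20 × √(2/27) = 0.054, so the shift is about half a standard error.

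**The case against.** **The link itself is not in the documents.** Background and Discussion cover prevalence, catheterisation, infection and quality of life, but not spontaneous bladder recovery or its timing. This stands. The point is conditional, and its size is an assumed range.

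**A reader might infer that the trial is underpowered.** The documents do not support this. It holds only in case B, and nothing printed says which case applies. The primary analysis is by intention to treat with imputation, so it may include close to 27 per arm. Unadjusted power then stays above 0.80 unless the link is strong.

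**A reader might infer that chance imbalance could bias the result.** It does not. Allocation is random, and the ordinary standard error of the two-sample comparison already allows for imbalance in prognostic factors. The imbalance figures describe sampling error that a covariate could reduce.

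**A reader might infer that patients only days after stroke will certainly enter, or that time since stroke is ignored altogether.** Item 8 of the exclusions is ambiguous and could imply a floor of about one week if it refers to stroke treatment. The window would still run from about one week to 2 years. Time since stroke is also used once, as the upper entry limit.

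**Covariates are often left to the SAP, and breadth looks deliberate.** The article declines to restrict by stroke type or region and aims to generalise. That is a good reason to leave entry alone. It does not answer the analysis point, because the article does not leave the test open: it names a two-sample test without covariates. Other baseline factors could also be proposed, but this one is already required for eligibility.

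**Conclusion.** The point holds as a matter of precision. The entry window is wide, and the article fixes a comparison that makes no use of where in that window a patient falls. The planned test is valid and unbiased.

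For R² between 0.05 and 0.36, adjustment adds roughly 2 to 14 percentage points of power at 21 per arm in case A (0.80 to 0.82–0.94). In case B it recovers roughly 2 to 19 points (0.78–0.61 back to about 0.80). At the low end the gain is negligible.

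The result rests on three assumptions: that the two-week change depends on time since stroke, the R² range, and a two-sided alpha. Confidence in the size is low. Confidence in what the article states is high, apart from the ambiguous wording of exclusion item 8.

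**What to change.** Before unblinding, prespecify time since stroke onset as a covariate in the primary comparison, alongside the baseline PVR ratio. Enter it as log days, or as early/late with the cut fixed in advance. If the non-parametric route is taken, use a rank test stratified by early/late. Record the stroke date at baseline, and tabulate the change in PVR ratio by arm within early and late patients. Leave the entry criteria unchanged.

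The cost is a line in the analysis plan and one degree of freedom for time since stroke (one more for the baseline ratio). No new visit or measurement is needed. If time since stroke is only weakly prognostic, little is gained and almost nothing is lost. The choice has to be made in advance, because adding the covariate after seeing an imbalance would be post hoc.
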